### Assignment of interventions: allocation

#### Sequence generation {16a}

All assignment to interventions has already been completed, and no new randomization will be necessary for this present protocol. In the first RCT from which participants will be drawn [15], participants were randomized using a randomization script in R (i.e., using computer generated random numbers), and were not stratified in any way. In the second RCT from which participants will be contacted [20], participants were randomized using a randomization script in R and were stratified by sex and by form (i.e., school grade). In the final RCT from which participants will be drawn [21], participants were randomized using an R script offsite by a third party, and randomization was stratified by sex and form and checked for balance on age, GAD, and PHQ baseline scores.

#### Concealment mechanism {16b}

All students included in these past three studies from which participants will be contacted [15, 20, 21] were randomized at one time per study using a computer-generated randomization sequence; thus, the study team had no way of knowing the allocation sequence prior to assigning participants to interventions and had no control over which participants were assigned to which intervention or control conditions.

#### Implementation {16c}

Participants from all three past RCTs included in this study were enrolled by members of the study team based in Kenya. In the third and largest RCT [21], an offsite researcher generated the allocation sequence in order to assign all participants to interventions. In the first two RCTs [15, 20], an onsite member of the study team generated the allocation sequence that was used to randomly assign participants to study conditions.

### Assignment of interventions: blinding

#### Who will be blinded {17a}

In all three past trials from which participants will be drawn, participants, lay-providers, and study staff working with participants could not stay blind to condition, however, they were kept blind to study hypotheses. Lay-providers and participants were not informed which groups were expected to be most effective and were told that the studies were intended to test different programs to improve wellbeing and academic performance. For the current trial, study staff collecting measures from participants will be kept blind to participant intervention condition.

#### Procedure for unblinding if needed {17b}

The only circumstance under which unblinding may become necessary is in case of an emergency (e.g., participant risk). If this occurs, the participant’s assessors will be kept blind to their condition, and other study staff and supervisors who are not collecting outcomes will be informed of the participant’s study condition if necessary.

### Data collection and management

#### Plans for assessment and collection of outcomes {18a}

Three-to-four years after participating in a Shamiri RCT, participants will complete a battery of assessments, to include outcomes from previous RCTs, as well as additional behavioral and health assessments. Primary outcomes include symptoms of depression (as measured by the PHQ-8), symptoms of anxiety (as measured by the GAD-7), academic performance (standardized scores representing grades), and personal satisfaction with social support (MSPSS). Secondary outcomes include character strengths (EPOCH), wellbeing (SWEMBS), sense of life purpose (PILS-12), gratitude (GQ-6), sense of primary and secondary control (PCSC, SCSC), quality of sleep (ASWS), alcohol and substance use (AUDIT, ASSIST), pregnancy and children, intimate partner violence, HIV status and risk behavior, HRV (smart watch measurement), physical activity (smart watch measurement), history of hospitalization, and vital and anthropometric measures. Socioeconomic status and demographics will also be collected (Household Wealth and Demographic questionnaires). Study measures, scales, and questionnaires are further detailed under {12}.

Self-reported measures, including primary measures of depression, anxiety, and social support will be collected from participants immediately following the consenting/assenting process. Consent/assent will be collected by a member of the study team, who will be trained to give information to the participants about what will be collected from them. Participants will then visit with a clinician for collection of more sensitive health and behavioral data. The clinician will be trained in and apply standard procedures for administration of all health and behavioral measures. All data will be entered into a tablet or computer upon collection, and each participant will be identified in this database only by their study ID. The study team will promote data quality by training the data collection team on adherence to study protocols and rules of trial conduct, including proper data collection techniques. All those who interact with private participant data will have up-to-date human subjects training certifications from the federal government. We will conduct periodic data entry checks and will use range checks on all continuous data points, as described under {19}.

#### Plans to promote participant retention and complete follow-up {18b}

Study team members will work with school officials to trace the contacts of participants in our previous trials. School officials will identify the current class of participants still in school and the phone numbers of participants who have graduated. The school staff will be compensated for their efforts to trace participants.

To encourage participation in our study, adults will be compensated with KES 500 (USD 5), in addition to reimbursement of travel and refreshments. Minors will be encouraged to participate with an incentive agreed upon with each individual school, as decided by school administrators. For example, one school wishes for student participants to be compensated with a KES 500 (USD 5) supermarket gift card. Among participants who wish to wear a smart watch for 2 weeks to provide additional health measures, adults will be provided with a KES 300 (USD 3) incentive and minors with a reward agreed upon by the staff at their school. Overall, the Shamiri program was well-received and participants were grateful to be involved. We hope to utilize this reciprocity when re-contacting participants.

#### Data management {19}

All follow-up data will be collected with a tablet or computer via KoBoToolbox (KoBo), an open-source data collection software developed by the Harvard Humanitarian Initiative [68]. Once the data is entered, it will reach a server physically located in Massachusetts, USA, where it will only be accessible with the Shamiri KoBo account username and password. The KoBo server administrator could access this data only if we give explicit instructions to do so. KoBo user passwords are stored fully encrypted on the KoBo server, using Django open-source framework. Django uses the PBKDF2 algorithm with a SHA256 hash, which is considered very secure. For additional caution, only participant’s study ID numbers, not participant names, will be stored on KoBo.

Upon recruitment into this study, all participants will be assigned a unique and de-identifying participant ID number. All follow-up data collected as part of this study will be associated with the participant’s unique ID. The database linking unique IDs with identifiable participant data will be stored electronically in an encrypted file using a separate password to protect participant identities. Only select study team members have access to data which identifies participants. Data access will be limited to study staff with IRB approval. Any team member who will conduct data collection or data entry will sign confidentiality agreements before handling data and receive formal training in the cruciality of participant confidentiality. All data points requiring the study team to enter a number will have range limits which have been pre-defined using the KoBo software. Full data entry and storage protocols to protect patient confidentiality are detailed in section {27} below.

#### Confidentiality {27}

We will separate information which identifies participants from sensitive participant data and make only fully de-identified data public. The database containing sensitive data will be associated with a participant ID which has been assigned by study staff. As noted above under {19}, we will use the software called KoBo Collect for data entry, which is fully compliant with the European Union’s General Data Protection Regulation. Once the data collection is complete and reaches the KoBo server, we will download the responses to a password-protected and encrypted database on our Shamiri server and delete them from the KoBo server once analyses are complete.

All study data will be de-identified and stored in a password-protected and encrypted database only accessible to study staff. Select members of the study team will have access to this database via confidential usernames and passwords. All information which identifies participants to sensitive study data will be stored in this password-protected and encrypted database. A list of participant names and corresponding study ID numbers will be stored in a separate, password-protected folder of Shamiri’s password-protected and encrypted electronic database. Any features which could potentially identify participants to their sensitive data will be removed from the aggregate data presented to those outside the study team (e.g., in presentations or manuscripts). The data collection team will know participant names and the information participants choose to share with them. The study clinician, who will collect the most sensitive health, behavior, and life outcome measures, will not have access to participant names or any identifiable data. However, the study clinician has received in-depth human subject protection training and will sign an agreement to adhere to confidentiality procedures applied in healthcare contexts.

#### Plans for collection, laboratory evaluation, and storage of biological specimens for genetic or molecular analysis in this trial/future use {33}

N/A; this trial does not involve collection or analysis of biological specimens.

#### Interim analyses {21b}

No interim analyses are planned while data collection is ongoing. However, because of the large number of study outcomes, results may be reported across more than one manuscript to enable thorough reporting. We do not have study stopping guidelines in place because we do not anticipate that the study will cause harm to participants. If individual participants appear to present with serious risk of harm to self or others, the expert clinicians involved in the study could decide to withdraw the participant from the trial and instead provide or refer to other more intensive or specialized resources.

#### Methods for additional analyses (e.g., subgroup analyses) {20b}

In secondary, exploratory analyses, we will compare long-term outcomes in the growth-only, gratitude-only, and sense of purpose-only interventions to long-term outcomes in the control group and in the Shamiri Intervention group. For these analyses, we will use the same model types as described above but using the corrections for multiple testing to keep the family-wise error rate. Additional analyses (e.g., mediator and moderator analyses, or analyses of baseline data) will be conducted in an exploratory fashion rather than as part of main analyses described in this protocol. Such exploratory analyses will be disseminated in separate publications from main analyses.

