**Methods:**

Three previous randomized controlled trials of the Shamiri intervention, a 4-week, group-delivered, lay-provider-led intervention, have been conducted in Kenyan high schools. Shamiri teaches positively focused intervention elements (i.e., growth mindset and strategies for growth, gratitude, and value affirmation) to target symptoms of depression and anxiety and to improve academic performance and social relationships, by fostering character strengths. In this long-term follow-up study, we will test whether these mental health, academic, social, and character-strength outcomes, along with related health outcomes (e.g., sleep quality, heart-rate variability and activity level measured via wearables, HIV risk behaviors, alcohol and substance use), differ between the intervention and control group at 3–4-year follow-up. For primary analyses (*N*_anticipated_ = 432), youths who participated in the three previous trials will be contacted again to assess whether outcomes at 3–4-year-follow-up differ for those in the Shamiri Intervention group compared to those in the study-skills active control group. Multi-level models will be used to model trajectories over time of primary outcomes and secondary outcomes that were collected in previous trials. For outcomes only collected at 3–4-year follow-up, tests of location difference (e.g., *t*-tests) will be used to assess group differences in metric outcomes and difference tests (e.g., odds ratios) will be used to assess differences in categorical outcomes. Finally, standardized effect sizes will be used to compare groups on all measures.

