### Trial design {8}

This study is a parallel-group randomized comparative effectiveness trial with five arms: (1) the Combined Shamiri Intervention (consisting of a growth element, a gratitude element, and a value affirmation element), (2) the Growth Intervention, which encompasses content related to growth mindset and strategies for growth, (3) the Gratitude Intervention, which incorporates content to build feelings of gratitude and expression of gratitude, (4) the Values Intervention, which incorporates content to help students identify, affirm, and better act on their personal values and sense of purpose, and (5) a Study Skills Control, an active control group teaching students study skills that may be useful to them as students. Each condition is described further in section {11a}. All participants in this trial have already completed intervention in these conditions in three previous RCTs. The first and second RCT had two conditions, the Combined Shamiri Intervention, and the Study Skills control, and these interventions were administered with a 1:1 ratio, or equal probability for assignment to each of the two conditions. In the third RCT, participants were allocated within each school to the five conditions with a 1:1:1:1:1 ratio or equal probability for assignment to each of the five conditions. Each arm required 4-h-long sessions spanning 4 weeks and was delivered in a group of 8–15 students by a local lay provider, aged between 18 and 24. Measures of mental health, wellbeing, and character strengths were collected in the three previous RCTs at baseline, 2-week midpoint, 4-week endpoint, and 1-month, 3-month, 7-month, and 9-month follow-up. For this long-term follow-up, measures of mental health, wellbeing, character strengths, stress, health behaviors, socioeconomic and health status will be collected at 3–4 years follow-up. Academic data was collected in the three previous RCTs for the school terms before, during, and immediately after the intervention. For the current trial, academic data will be collected for the last year of secondary school. De-identified trial data will be available upon request.

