#### Participant timeline {13}

The participants in this study have already completed interventions as part of three previous RCTs testing Shamiri [15, 20, 21]. As part of the current RCT, participants will be contacted again for long-term follow-up. Per Table 1, participants from the first cohort completed the intervention in June 2018 and will be contacted for informed consent in January 2022. Immediately following consent, these participants will complete a battery of long-term follow-up measures, to include primary measures which have been collected as part of the previous trial, secondary self-report measures, some of which were collected in this trial, and additional health and behavioral measures which have not been collected before. Participants in the second cohort completed the intervention in July and August 2019 and will be contacted to provide informed consent to participate in this study in September and October 2022. Immediately following consent, participants will complete all follow-up measures as part of this study in September and October 2022. Participants who are part of the third RCT completed the intervention between May and July 2021. These participants will be contacted for consent to participate in this study between August and November 2024 and will complete follow-up measures which are part of this study immediately following their consent.

**Table 1 Tab1:** Schedule of previous intervention implementation and study follow-up outcome measures

Time point	STUDY PERIOD												
	Enrolment			Allocation			Post-allocation						Close-out
	Jun 2018	Jun-Jul 2019	May 2021	Jun 2018	Jul 2019	May 2021	Jun 2018	Jul-Aug 2019	May-Jul 2021	Jan 2022	Sep-Oct 2022	Aug-Oct 2024	Nov 2024
**ENROLMENT**^**a**^													
Eligibility screen	x	x	x										
Informed consent	x	x	x							x	x	x	x
Allocation				x	x	x							
**INTERVENTIONS**^**a**^													
Combined Shamiri							x	x	x				
Growth									x				
Gratitude									x				
Values									x				
Study skills control							x	x	x				
**ASSESSMENTS**^**b**^													
Demographic characteristics										x	x	x	x
Depression, anxiety, perception of social support										x	x	x	x
Gratitude, purpose, perceived and secondary control, wellbeing, character strengths										x	x	x	x
Anthropometric measures										x	x	x	x
HIV risk behaviors and status											x	x	x
Household wealth										x	x	x	x
Intimate partner violence											x	x	x
Alcohol and substance use										x	x	x	x

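### As written, the exploratory single-component contrasts draw comparators from all three RCTs, although those arms were randomised only in the third

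*Protocol article*

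**What the plan says.** Trial design {8} presents the follow-up as one study: "This study is a parallel-group randomized comparative effectiveness trial with five arms". The same section shows where the arms come from. On the two earlier trials: "The first and second RCT had two conditions, the Combined Shamiri Intervention, and the Study Skills control". On the last: "In the third RCT, participants were allocated within each school to the five conditions with a 1:1:1:1:1 ratio". Table 1 agrees. It marks growth, gratitude and values only for the 2021 trial, and combined Shamiri and study skills for all three.

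The two main groups are built from every trial. The abstract states that "youths who participated in the three previous trials will be contacted again to assess whether outcomes at 3–4-year-follow-up differ", and Sample size {14} adds the three RCTs together to reach about 720 eligible and 432 followed up.

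Section {20b} then sets the single-component arms against these groups: "we will compare long-term outcomes in the growth-only, gratitude-only, and sense of purpose-only interventions to long-term outcomes in the control group", and likewise in the full Shamiri group. (I take the purpose arm to be the Values arm of {8}.) On the model it says "we will use the same model types as described above but using the corrections for multiple testing". The models it refers to, in {20a}, have random effects for lay-provider, school, group and individual. Random slopes are only a variation that may be tried. Outcomes first measured at follow-up may be adjusted, probably for age, gender and school. No model includes trial or cohort.

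On timing, Participant timeline {13} says "Participants who are part of the third RCT completed the intervention between May and July 2021", with follow-up in August–November 2024. The first two cohorts were treated in June 2018 and July–August 2019 and are followed up in January 2022 and September–October 2022.

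**The concern.** A participant in the first or second RCT had no chance of receiving a single component. If such participants sit in the comparator, part of the contrast is randomised and part is a comparison with a different cohort, treated two to three years earlier and assessed about two years earlier. The protocol's own background says that reports of youth mental health problems are rising, especially because of the COVID-19 pandemic, so a cohort difference in trajectory is plausible. The Discussion concedes that measurement timing differs between cohorts and treats this as a threat to internal validity, but draws no consequence for these contrasts.

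At stake is the interpretation of the component comparisons. A difference between cohorts could be reported as a long-term effect of growth, gratitude or values content, or could hide one.

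**Working it through.** **The plan's own figure.** 720 × (1 − 0.40) = 432, as stated in {14}. Split evenly, 216 v 216, the detectable difference is (1.960 + 0.842) × √(1/216 + 1/216) = 0.27 SD (two-sided 5%, 80% power, no allowance for clustering or repeated measures). This is a plausible reading of a small-to-medium effect, which the protocol does not give as a number.

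**Inputs from the document.** First RCT 51 and second RCT 413 (Background {6a}), total 464, allocated 1:1. The third RCT is called the largest (Implementation {16c}), but its size is not given.

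**Assumptions.** The ~720 covers the Shamiri and control arms only. Retention is 60% in every trial and arm, so attrition does not change the shares.

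**Non-concurrent share of the comparator (per arm, before attrition).**
- All 464 eligible: 464/2 = 232 from the first two RCTs and (720 − 464)/2 = 128 from the third. Share = 232/360 = 0.64.
- Only 300 eligible (assumed): 300/2 = 150 and (720 − 300)/2 = 210. Share = 150/360 = 0.42.

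**Bias.** Let w be the non-concurrent share and δ the difference between the earlier cohorts and the third, in SD of the tested quantity. The comparator mean moves by w × δ, so an unadjusted contrast is biased by w × δ. All values of δ are assumed.

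| δ (SD) | Bias, w = 0.64 | Bias, w = 0.42 |
|---|---|---|
| 0.1 | 0.06 | 0.04 |
| 0.2 | 0.13 | 0.08 |
| 0.3 | 0.19 | 0.13 |

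**Effect on type I error, w = 0.64.** After attrition the contrast is 128 × 0.6 = 77 against 360 × 0.6 = 216. Its standard error is √(1/76.8 + 1/216) = 0.133. Dividing each bias by 0.133 and using the normal approximation, the nominal 5% becomes about 8%, 16% and 31% for δ = 0.1, 0.2 and 0.3.

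**What the planned model removes.** For outcomes measured repeatedly, which include all four primary outcomes, {20a} tests condition over time. A constant level difference between cohorts does not enter that test, so δ is a difference in change. A random school intercept acts on level and does not remove a difference in change. For outcomes measured only at follow-up, δ is a difference in level. School terms can absorb some of that, depending on whether the trials used different schools, which the document does not say. The standardised effect sizes are described as mean gain scores with no adjustment named, so the unadjusted figures apply most directly there.

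**The case against.** The strongest reply is that pooling is inferred. Section {20b} does not use the word, the abstract's statement about drawing on all three trials concerns the primary analyses, and {20b} carries over model types rather than an analysis set. A later analysis plan could restrict these contrasts to the third RCT. Section {8} also discloses the two-arm and five-arm structure openly. This stands as a limit on certainty. It does not remove the point, because {20b} already names comparators and model, uses the group names defined over all three trials, and sets no restriction.

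Several stronger readings are tempting, and the documents do not support them:

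- *The primary contrast is confounded too.* It is not. Allocation between Shamiri and control was equal in every RCT, so trial does not confound that comparison.
- *Every cohort difference becomes a component effect.* Only a difference in change does so for repeatedly measured outcomes. Level matters only for outcomes first measured at follow-up.
- *Most comparators are known to be non-concurrent.* The 232 per arm is an upper bound, and under the assumed 300 eligible the share falls below half. A share of 82% (232/283) results if ~720 covers all five arms, but that leaves 720 − 464 = 256 in the third RCT, which is hard to square with its being the largest.
- *The bias is close to what the trial can detect.* The 0.27 SD belongs to the primary contrast. For 77 v 216 the detectable difference is 0.37, so even 0.19 is about half of it.
- *This is the only analysis that addresses components.* The Background says the third RCT itself is meant to do so.

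**Conclusion.** The point holds for the exploratory single-component contrasts. As written, they mix randomised comparators with participants from earlier trials, and the stated models correct for this only in part. The non-concurrent share is about 64% if all 464 earlier participants are eligible and ~720 covers two arms, and about 42% if 300 are eligible. The resulting unadjusted bias is roughly 0.04 to 0.19 SD for assumed cohort shifts of 0.1 to 0.3 SD, in either direction. The shares and shifts are assumptions, and the planned models would reduce the bias by an unknown amount. The arm structure itself is explicit in the protocol. The matter deserves correction because a fully randomised comparison already exists inside the third RCT. It does not threaten the primary conclusion.

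**What to change.** State in {20b} that every contrast involving a single-component arm uses third-RCT participants only. Alternatively, include trial and trial-by-time fixed effects (trial alone for outcomes measured only at follow-up), so that the contrast is estimated within the third RCT. No trial term is needed in the Shamiri-versus-control model on this ground.

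The cost is precision in exploratory contrasts. In the 64% case the comparison becomes 77 v 77, with a detectable difference of 2.802 × √(2/76.8) = 0.45 SD instead of 2.802 × √(1/76.8 + 1/216) = 0.37 SD, before the planned multiplicity correction.
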